**Methods and Design:**

Sixty eligible participants will be recruited and randomly assigned into treatment group (He's* Santong* needling method and swallowing rehabilitation training) and control group (swallowing rehabilitation training) in a 1:1 ratio. All treatments will be provided everyday on weekdays with a two-day interval at the weekend, during a total treatment course of four weeks. The Penetration-Aspiration Scale with Fiberoptic Endoscopic Examination of Swallowing will be assessed at baseline and endpoint (Week 4) as primary outcomes. The Saitoh's classification score, Swallowing-Related Quality of Life score, the Modified Mann Assessment of Swallowing Ability score, and Surface Electromyography will be evaluated at baseline and endpoint as secondary outcomes.

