## 1. Background

Dysphagia after stroke, manifested as difficulty in swallowing, is a common complication affecting between 37% and 78% of stroke patients [1]. Although the majority of patients achieve recovery from dysphagia spontaneously, dysphagia is still present in 11–50% of stroke sufferers at six months after stroke onset. Persistent dysphagia puts them at risk of pneumonia, malnutrition, dehydration, and even death [2]. It has been confirmed that the existence of dysphagia is associated with poor outcome during the subsequent years [3].

Swallowing is considered one of the most complex neuromuscular activities, which involves 26 pairs of muscles, five cranial nerves, and a complex neural network which coordinates swallowing muscles [4]. Sensory input from the oral cavity, pharynx, and larynx to the central pattern generator (CPG) has been shown to affect swallowing initiation, facilitation, and airway protection [5]. Dysphagia after stroke is thought to be due to damage to the swallowing-related cortex and subcortical structures. The recent researches have demonstrated that increased sensory input can drive long-term beneficial neural changes and reorganize brain plasticity of the swallowing cortex [6].

In order to improve the recovery and shorten the recovery time, various therapeutic options exist for dysphagia after stroke, including exercise-based rehabilitation, drugs, surgical rehabilitation, noninvasive brain stimulation (NBS), and neuromuscular electrical stimulation (NMES) [7]. There is no recommended routine clinical treatment for dysphagia after stroke, although several studies have shown that each approach appears to be promising [2, 7]. Effective alternative therapies are needed to be developed.

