### 2.4. Participants

#### 2.4.1. Inclusion Criteria

Participants who meet all of the following requirements will be allowed for enrolment: (1) aged between 18 and 80 years old, (2) diagnosed as having ischemic stroke which confirmed by a CT or MRI scan, (3) identified as clinical dysphagia using Kubota water swallowing test (level 3, 4, or 5), (4) the symptoms of dysphagia lasting over two weeks to three months after stroke onset, and (5) absence of cognitive impairment (score of the abbreviated mental test (AMT) >=8).

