### 2.11. Sample Size

This pilot study is to evaluate the effect of He's* Santong* needling method on dysphagia after stroke. However, no previous study was found on the effect of acupuncture on the PAS with FEES. A sample size of 30 per group was regarded as a reasonable minimum recommendation for a pilot study [36]. Therefore, we plan to recruit 60 participants.

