### 2.12. Statistical Analysis

Statistical analysis will be performed by statisticians that are blind to allocation of group and intervention process. SPSS 22.0 software (International Business Machines Corporation) will be used for statistical analysis. The intention-to-treat population will be the main set for all efficacy analysis. This population will consist of all randomly allocate participants regardless of the type of treatment received. The per-protocol set will be utilized for sensitivity and consistency analysis to compare the results from the intention-to-treat set. All statistical tests will be two-sided, and p<0.05 is considered statistically significant.

One sample of the Kolmogorov-Smirnov test will be used to test the normal distribution of continuous variables. Continuous variables will be shown as means± Standard deviations (SDs) if they are normally distributed or as medians with IQRs if they are not normally distributed. If the measurement data have normal distribution, independent two-sample* t*-tests will be used for comparisons among the groups, while paired* t*-tests will be used for within-group comparisons. If the measurement data are not normally distributed, the Mann–Whitney* U* test will be used for comparisons among the groups, while Wilcoxon signed-ranks test will be used for within-group comparisons.

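### Within-arm significance tests are planned without saying that efficacy rests on the between-group comparison, in a setting where both arms are expected to improve anyway

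*Protocol article*

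**What the plan says.** Section 2.12 (Statistical Analysis) of the protocol article gives two pairs of tests and chooses between them by a normality check. For normal data, an independent two-sample t-test compares the groups and a paired t-test is applied within each group. For non-normal data, the Mann–Whitney U test compares the groups and the "Wilcoxon signed-ranks test will be used for within-group comparisons". One rule covers all four: "All statistical tests will be two-sided, and p<0.05 is considered statistically significant". The section does not rank the between-group test above the within-group tests, and does not call the latter descriptive.

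Three other sections bear on what a within-arm change can mean:

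- Section 1 (Background): "Although the majority of patients achieve recovery from dysphagia spontaneously".
- Section 2.4.1 (Inclusion Criteria) requires "the symptoms of dysphagia lasting over two weeks to three months after stroke onset".
- Section 2.7 (Interventions) gives swallowing rehabilitation training to both arms for four weeks, so the control arm is actively treated.

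Outcomes are measured at Week 0 and Week 4 only (section 2.8.2 and Table 1).

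**The concern.** A within-arm test asks whether that arm changed from baseline. The trial asks whether adding needling changes the result. Where recovery over time and rehabilitation are at work in both arms, the hypothesis of no change within an arm is implausible from the start, and rejecting it tells the reader nothing about needling.

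Setting the two within-arm p-values side by side does not repair this. A significant change in one arm and a non-significant change in the other is not a test of the difference between the arms. With a modest true change common to both, chance alone often puts one p-value below the threshold and the other above it. If a report leaned on that contrast, or simply on a significant needling-arm change, it could present recovery and rehabilitation as a needling effect.

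**Working it through.** **Inputs from the protocol**

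- Two-sided alpha 0.05 (section 2.12).
- 30 per group (section 2.11: "A sample size of 30 per group was regarded as a reasonable minimum recommendation for a pilot study"), allocated 1:1. The stated total reproduces: 30 × 2 = 60. It is a rule of thumb, so there is no power figure to reproduce.

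**Input assumed**

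- The standardised change d, meaning mean change divided by the SD of change, is the same in both arms (no needling effect). The protocol gives no expected change or SD for the Penetration-Aspiration Scale (PAS), so d is varied from 0 to 1.0. All 30 per arm are taken to have both assessments.

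**Step 1. Chance that one arm shows a significant improvement.** For a paired t-test with n = 30, the critical value is t(0.975, 29 df) = 2.045 and the noncentrality is d√30. Let p be the probability that a noncentral t with that noncentrality exceeds 2.045. For d = 0.5, d√30 = 2.739 and p = 0.754.

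**Step 2. Chance of the misleading pattern.** The arms are independent and, under no effect, share the same p:

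- needling significant, control not: p(1 − p)
- discordant in either direction: 2p(1 − p)
- both significant: p²

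| d | p | needling only | either discordant | both |
|---|---|---|---|---|
| 0 | 0.025 | 2.4% | 4.9% | 0.1% |
| 0.1 | 0.076 | 7.1% | 14.1% | 0.6% |
| 0.2 | 0.184 | 15.0% | 30.0% | 3.4% |
| 0.3 | 0.355 | 22.9% | 45.8% | 12.6% |
| 0.37 | 0.50 | 25.0% | 50.0% | 25.0% |
| 0.5 | 0.754 | 18.6% | 37.1% | 56.8% |
| 0.6 | 0.888 | 9.9% | 19.9% | 78.8% |
| 0.7 | 0.959 | 3.9% | 7.8% | 92.1% |
| 0.8 | 0.988 | 1.1% | 2.3% | 97.7% |
| 1.0 | >0.999 | <0.1% | 0.1% | 99.9% |

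The product p(1 − p) cannot exceed 0.25, reached at p = 0.5, so 25% is the ceiling for any d. The table counts significant improvement only. If significance in either direction is counted, p at d = 0.1 becomes 0.083 and the pattern 0.083 × 0.917 = 7.6%. From d = 0.2 upward the two counts agree to within 0.1 percentage point.

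**Step 3. Cross-check on an ordinal scale with the planned rank tests.** An eight-level score was simulated with identical distributions in both arms (baseline uniform on levels 3 to 8; Week 4 equal to baseline minus a common shift plus normal noise with SD 2, rounded and held within 1 to 8; 3,000 runs per scenario). Wilcoxon signed-rank was applied within arms and Mann–Whitney to the change between arms.

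| mean change | SD of change | needling only (Wilcoxon) | between-group (Mann–Whitney) |
|---|---|---|---|
| −0.20 | 1.69 | 7.9% | 4.2% |
| −0.60 | 1.71 | 24.2% | 4.5% |
| −0.80 | 1.72 | 21.9% | 4.6% |
| −0.99 | 1.72 | 11.9% | 4.7% |
| −1.41 | 1.71 | 0.7% | 4.7% |
| −1.81 | 1.68 | 0.0% | 4.5% |

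The rank tests behave like the paired t calculation, and the between-group test keeps close to its 5% rate throughout. Section 2.12 does not say whether the between-group test is applied to change or to Week 4 values. Change was used here.

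**The case against.** The strongest reply is that no faulty inference is written down. The design is a 1:1 randomised comparison, section 2.12 names the between-group test first in each pair, and the sentence on p<0.05 sets a threshold, not an order of inference. An analysis plan that is not shown may label the within-arm results descriptive. This stands as a limit on the point. A reader might infer that the investigators intend to read efficacy from the within-arm pattern, or that those p-values will become the headline. The article says neither. What remains is that it prescribes these tests as significance tests and does not subordinate them.

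The second reply is that the rate depends on an assumed change and that d from 0.3 to 0.5 brackets the worst case. That is right, which is why the full range is shown. There is also a tension in the argument: if recovery and rehabilitation are strong, both arms will be significant and the discordant pattern almost disappears. The problem then changes form, since at d = 0.8 the needling arm is significant in 98.8% of trials with no needling effect at all.

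Third, the Background statement about recovery concerns post-stroke dysphagia in general, while this trial enrols patients whose symptoms have lasted more than two weeks. How far they recover over four weeks is inferred, not stated. The active treatment of both arms supports the expectation of change independently.

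A reader might also count the five outcomes as five chances of error. PAS is the single primary outcome, the other four are secondary and probably correlated, and no joint probability was calculated, so that claim is not made.

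**Conclusion.** The point holds as a risk of misinterpretation. The planned within-arm tests cannot answer the trial's question, because change is expected in both arms without needling, and section 2.12 does not say that conclusions rest on the between-group test.

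With no treatment effect and 30 per arm, the chance that needling alone reaches significance runs from about 7% to 8% at a common standardised change of 0.1, through a maximum of 25% near 0.37, to 10% at 0.6 and 1% at 0.8. A valid two-sided 5% test would err in that direction 2.5% of the time. These figures assume equal change in both arms, complete data and a range of d that the protocol does not supply. At no value of d does within-arm significance bear on needling.

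A reader might go further and conclude that the primary comparison is invalid. It is not: a valid between-group test is planned, and its simulated false-positive rate is 4.2% to 4.7%.

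**What to change.** In section 2.12, remove the paired t-test and the Wilcoxon signed-rank test. Report the change within each arm descriptively, as a mean or median with a 95% confidence interval and no p-value.

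Add a statement that conclusions about needling rest only on the between-group comparison of Week 4 outcomes, adjusted for the baseline value of the same measure. This could be ANCOVA for the continuous outcomes and an ordinal or rank-based equivalent for PAS, reported as an estimate with its confidence interval.

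The cost is one added model per outcome, a choice of model for the eight-level PAS, and the loss of the within-arm p-values. Baseline and Week 4 values are already collected on every outcome, so no visit, measurement or participant is added. If the within-arm tests were kept, the statement about where conclusions rest would still remove most of the risk.

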### 2.13. Ethics and Dissemination

The trial protocol has been approved by the Research Ethical Committee of Beijing Hospital of Traditional Chinese Medicine Affiliated to Capital Medical University on 9 May 2017 (ethical batch number: 2017BL-013-02). This trial was registered at ISRCTN (ISRCTN68981054). Each participant will be notified regarding the study protocol. Written informed consent will be obtained from each participant.

## 3. Discussion

Evidence accumulating from clinical trials has indicated that acupuncture is effective for dysphagia after stroke [14]. In clinical practice, combined acupuncture technique has been widely used to enhance the acupuncture effect. However, the combined acupuncture technique studies are still lacking. Therefore, we design this pilot study to evaluate the effectiveness of He's* Santong* needling method for dysphagia after stroke. The advantages of the trial design are shown in the following two aspects.

### 3.1. Comprehensive Outcome Measures

Instrumental evaluation of dysphagia mainly includes videofluoroscopy swallowing study (VFSS) and FEES. Considering the feasibility, the PAS with FEES is to be selected as the primary outcome. Combined with PAS, FEES is demonstrated as having a high level of agreement with VFSS [31]. Furthermore, VFSS cannot be used at the bedside frequently for follow-up tests because of the necessary exposure to radiation [37]. Compared with VFSS, the FEES is a more appropriate assessment tool for dysphagia assessment after stroke, especially for our study which concerns oral and pharyngeal phase of swallowing [38, 39]. For stroke patients, a bedside test will ensure patient's comfort and compliance.

Saitoh's classification of dysphagia, SWAL-QOL, MMASA, and sEMG will be used as secondary outcome. Saitoh's classification of dysphagia is an ordinary tool to assess the swallowing function of a patient, which has been utilized to evaluate swallowing function in dysphagia patients [32]. SWAL-QOL is a valid, effective, and sensitive tool to assess quality of life of people with dysphagia, which has been used in many studies involved dysphagia management [33]. The MMASA is a useful screening tool for evaluating eating and swallowing functions, which showed relatively high sensitivity and specificity for detecting aspiration [34]. The sEMG is a noninvasive assessment to monitor electromyographic signal of submental muscles, so it is a safe and repeatable method for stroke patients to evaluate strength of swallowing muscles [35].

### 3.2. Combined Acupuncture Technique

It has been demonstrated that ordinary acupuncture is an effective and safe treatment for dysphagia after stroke [40]. Compared with ordinary acupuncture, He's* Santong* needling method (*Weitong* (normal needling),* Wentong* (fire needling), and* Qiangtong* (bloodletting)) is a combined acupuncture technique, which is often applied to complications after stroke. For effective aspect, He's* Santong* needling method has the potential to increase therapeutic efficacy for dysphagia after stroke, since it combines three monotherapies. For safety aspect, fire needling and bloodletting have been widely used in China for thousands of years [23]. A set of national standard* standardised manipulations of acupuncture and moxibustion* has been established to ensure the safety of acupuncture techniques including bloodletting and fire needling (GB/T 21709.12-2009 and GB/T 21709.4-2008) [28].

It should be noted that our study has certain methodological limitation. Blinding is a crucial measure to assure the quality of the trial. As a limitation, it is difficult to implement blinding in participants because we will adopt a special acupuncture method. In order to overcome this problem, we will minimize the interaction between the participants and acupuncturists. In addition, all outcome assessors and statisticians will be kept blind throughout the whole process.

To our knowledge, this trial is the first attempt to investigate the efficacy of He's* Santong* needling method on dysphagia after stroke. The results of this trial may develop the clinical treatment of dysphagia. However, the biological mechanism of this therapy requires further investigation.

## Figures and Tables

**Figure 1 fig1:**
[figure not shown]
Flowchart of the trial protocol.

**Figure 2 fig2:**
[figure not shown]
Acupuncture points used in He's* Santong* needling method.

**Table 1 tab1:** Schedule of enrolment, interventions, and assessments.

**Baseline**		**Treatment**			
		**week 1**	**week 2**	**week 3**	**week 4**
**Enrolment**	****				
**Eligibility screen**	**×**				
**Informed consent**	**×**				
**Allocation**	**×**				
**Interventions**					
**Treatment group**					
**Control group**	****				
**Assessments**	****				
**PAS with FEES**	**×**				**×**
**Saitoh's classification**	**×**				**×**
**SWAL-QOL**	**×**				**×**
**MMASA**	**×**				**×**
**sEMG**	**×**				**×**
**Adverse events**	****				

## Data Availability

The data used to support the findings of this study are available from the corresponding author upon request.

## Abbreviations

AEs: Adverse events
AMT: The abbreviated mental test
CPG: Central pattern generator
FEES: Fiberoptic Endoscopic examination of Swallowing
MMASA: The Modified Mann Assessment of Swallowing Ability
NA: Nucleus ambiguous
NBS: Noninvasive brain stimulation
NMES: Neuromuscular electrical stimulation
NTS: Nucleus tractus solitaries
PAS: Penetration-Aspiration Scale
sEMG: Surface Electromyography
SWAL-QOL: Swallowing-Related Quality of Life
VFSS: Videofluoroscopy swallowing study.
